### Outcome measures

The primary endpoint of this study was the rate of MACCE, a composite ischemic vascular event following PCI, including cardiac death, nonfatal MI, TLR and ischemic stroke at 6 months in the DAT and TAT group. The key secondary endpoints defined a priori are

- P2Y12 reaction unit (PRU) as assessed by VerifyNow^® ^P2Y12 assay

- Cardiac death, nonfatal MI, TLR, target vessel revascularization (TVR), stent thrombosis and ischemic stroke

- MACCE according to the type of statin and its interaction with clopidogrel

- Bleeding, as defined according to the TIMI bleeding classifications [22], major bleeding defined by the presence of at least 1 of the following: intracranial bleeding (documented with magnetic resonance imaging, computed tomography, any other examination or autopsy), or clinically overt bleeding resulting in a 5 g/dL decrease in hemoglobin value (or, when hemoglobin values were not available, a 15% decrease in hematocrit).

- Angiographic outcome, such as late luminal loss, binary restenosis at 6 months' follow-up angiography

- Albumin-to-creatinine ratio

### Statistical Analysis

#### Sample size calculation

To test the hypothesis that TAT is superior to DAT in reducing MACCE at 6 months after PCI, based on the previous outcome data [10,13,23], we assumed that MACCE rate in DAT and TAT group would be 10% and 5% respectively. Using a superiority design, an estimated total of 960 patients was needed to ensure a power of at least 80% to detect a 5% difference in the composite of ischemic vascular events between the two anti-platelet therapy groups using a two-sided t-test, with a sampling ratio of DAT:TAT at 1:1, bilateral risk set at 5% and drop-out rate estimated to be 10%.

#### Statistical Analyses

All analysis will be done by intention-to-treat method (all patients analyzed as part of their assigned treatment group). However, per protocol (patients analyzed as part of their assigned group only if they actually received their assigned treatment) and as-treated analysis will also be performed solely for descriptive comparison.

The primary endpoint of 6 months' MACCE will be analyzed using χ^2^-test on an intention-to-treat analysis. The hypothesis will be evaluated based on a superiority testing. The clinical secondary endpoints will also be tested based on χ^2^-test, similarly as primary endpoint testing. The endpoints will be analyzed in pre-specified subgroups, which includes the presence of diabetes mellitus, long lesions (lesion length≥28 mm), small vessel lesions (lesion diameter < 2.75 mm), age and sex. Also, most importantly, post-hoc analysis of MACCE according to the type of statin given (atorvastatin vs. rosuvastatin) will be done. Analysis of platelet function will be tested using repeated ANOVA method with the Bonferroni's correction.

Continuous variables will be presented as mean ± SD and compared with the use of unpaired Student's t-test or in the case of non-normal distribution, Mann-Whitney U test. Categorical variables will be summarized as number or percentages and compared with χ^2 ^or Fisher's exact test, as appropriate. Survival curves using all available follow-up data will also be constructed for time-to-event variables using Kaplan-Meier estimates and compared by log-rank test. A p-value < 0.05 will be considered statistically significant.

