### Patient population

Patients at least 18 years of age who had typical ischemic symptoms or positive stress test and a native coronary lesion (≥50% diameter stenosis by visual estimation on coronary angiogram and reference diameter≥2.5 mm)) were included in this study. Five high-volume centers in Korea participated and enrolled the patients in this multicenter, open-label, prospective, randomized trial. There were nearly no angiographic limitations about the number of lesions, vessels, location of lesions or their length, to investigate the effect of cilostazol in the real-world setting. The following patients were excluded from the study; cardiogenic shock; explicit side effect or contraindications to anti-platelet agents including cilostazol; concomitant treatment with any other anti-platelet agent or anticoagulant other than the study drugs; current user of cilostazol before the entry of study. The detailed inclusion and exclusion criteria are summarized in Appendix 2.

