### Randomization and interventions

All patients received 300 mg aspirin and 300~600 mg clopidogrel loading before the procedure unless the patient had been taking these medications for at least 1 week before the procedure. Patients were randomized to receive either conventional DAT or TAT and also, randomly stratified to take equipotent doses of either atorvastatin 20 mg or rosuvastatin 10 mg per day before the interventional procedure. The patients were also stratified according to the enrolling medical centers/hospitals. A loading dose of cilostazol (Otsuka Korea) 200 mg was given immediately before the procedure. Random allocation of the patients was done via a Web-based computerized program separately managed at medical research collaboration center, Seoul National University Hospital. PCI was done according to the standard technique and the decision of the pre-dilatation and use of glycoprotein IIb/IIIa inhibitors were up to the operator's discretion. The target lesion/vessel was designated as the first lesion/vessel that was intervened. Platelet reactivity was measured by using the Ultegra Rapid Platelet Function Assay (VerifyNow^® ^Aspirin and VerifyNow^® ^P2Y12 assay, Accumetrics Inc., San Diego, California, USA) immediately before discharge.

After enrollment and index PCI procedure, clinical follow-up was planned at 1, 3, 6 months and all patients were recommended follow-up coronary angiography at 6 months according to local clinical practice. Platelet reactivity was also measured at 6 months after index procedure. The investigators were urged to follow the patients, either by office visits or by telephone contacts as necessary. Patient adherence to the study drug was checked at every outpatient visit and the decision of the drug discontinuation was always discussed and checked under the physician's recommendation.

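### The primary 6-month MACCE test is a crude chi-square that leaves out the randomization factors; the cost is small, and a stratified test would remove it

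*Protocol article*

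**What the plan says.** All places are in the protocol article.

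- **Primary test** (Statistical Analyses): "The primary endpoint of 6 months' MACCE will be analyzed using χ^2^-test on an intention-to-treat analysis". No stratification or adjustment is named.
- **Analysis set** (same section): "All analysis will be done by intention-to-treat method (all patients analyzed as part of their assigned treatment group".
- **Allocation** (Randomization and interventions): patients were randomized to dual (DAT) or triple (TAT) therapy and were "randomly stratified to take equipotent doses of either atorvastatin 20 mg or rosuvastatin 10 mg per day". In addition, "The patients were also stratified according to the enrolling medical centers/hospitals".
- **Number of centers** (Patient population): "Five high-volume centers in Korea participated and enrolled the patients".
- **Sample size** (Sample size calculation): "we assumed that MACCE rate in DAT and TAT group would be 10% and 5% respectively", at least 80% power, 1:1 allocation, "bilateral risk set at 5% and drop-out rate estimated to be 10" per cent, total 960.
- **Time-to-event analysis** (Statistical Analyses): "Survival curves using all available follow-up data will also be constructed for time-to-event variables using Kaplan-Meier estimates", compared by log-rank test. No 6-month limit is given. The abstract plans further MACCE checks at 1, 2 and 3 years.

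**The concern.** When randomization is stratified, the arms are balanced on the stratum factors by design. A test that ignores those factors leaves the between-stratum variation in its standard error, although balance has already removed that variation from the treatment difference. The standard error is then too large, so the test rejects too rarely when there is no effect and loses some power when there is one. How much depends on how far the event rate differs between strata.

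A second, smaller matter concerns follow-up. The sample size is inflated as if drop-outs contribute nothing, while the analysis sentence keeps every patient. The one planned method that uses partial follow-up runs over the whole follow-up, although triple therapy lasts only 6 months. As worded, it answers a different question from the primary endpoint and does not support it directly.

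**Working it through.** **1. The plan's own sample size.** With p1 = 0.10, p2 = 0.05, two-sided 5% and 80% power:

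n per arm = (1.960 + 0.842)² × (0.10×0.90 + 0.05×0.95) / 0.05² = 7.849 × 0.1375 / 0.0025 = 431.7, so 432.

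Total 864, and 864 / 0.9 = 960. The stated figure reproduces exactly, so the calculation treats 96 patients as not evaluable. Power by the pooled two-proportion formula is 79.8% with 432 per arm and 83.8% with 480 per arm and complete outcomes.

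**2. Effect of ignoring the strata when there is no treatment effect.** Assume ten equal strata (5 centers × 2 statins), 48 patients per arm in each, and a mean control rate of 10%. The documents give no stratum rates, so the spreads below are assumptions. The crude test uses the variance term 0.10 × 0.90 = 0.09. The true term under stratified allocation is the mean of p(1−p) over strata. With R the ratio of the true term to 0.09, the crude type I error is about 2 × [1 − Φ(1.96/√R)].

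- Rates 6% to 14%: mean p(1−p) = 0.0893, R = 0.993, type I error 4.9%.
- Rates 2% to 18%: mean 0.0874, R = 0.971, type I error 4.7%.
- Half at 1%, half at 19%: mean (0.0099 + 0.1539)/2 = 0.0819, R = 0.910, type I error 4.0%.

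**3. Simulation of both tests.** 200,000 trials per row, 480 per arm, no continuity correction. Power is shown for a risk ratio of 0.5 and for a common odds ratio of (0.05/0.95)/(0.10/0.90) = 0.474.

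| Control rates across strata | Type I, crude / CMH | Power, risk ratio 0.5, crude / CMH | Power, odds ratio 0.474, crude / CMH |
|---|---|---|---|
| 10% in all | 5.0% / 5.0% | 84.7% / 84.5% | 84.6% / 84.4% |
| 6% to 14% | 4.9% / 5.0% | 84.8% / 84.8% | 84.4% / 84.4% |
| 2% to 18% | 4.7% / 5.0% | 84.9% / 85.3% | 83.5% / 83.9% |
| Half 1%, half 19% | 3.9% / 4.9% | 85.4% / 86.8% | 81.2% / 82.9% |

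The largest loss is 1.4 points with a constant risk ratio and 1.7 points with a constant odds ratio. If the strata do not differ at all, CMH costs about 0.2 points. Smaller runs of 40,000 trials gave the same picture: crude type I error 4.8% at the 6% to 14% spread, and 3.8% to 3.9% at the extreme.

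**4. Follow-up.** Setting the sections side by side, the sample size implies 864 evaluable patients and the intention-to-treat sentence implies 960. Drop-out is not defined, and the only method able to use partial follow-up is not tied to 6 months.

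**The case against.** The strongest reply is that nothing here is an error. An unstratified test after stratified randomization is valid. It errs on the safe side and cannot manufacture a false positive. At plausible spreads the gain from CMH is nil, and the 1.7 points need an extreme spread that no section supports. All of this stands, and it is why the point is small. It does not answer why the plan should leave out factors it already randomizes by, when using them is essentially free.

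A reader might go further and infer that the chi-square cannot be an intention-to-treat analysis, because the expected drop-outs must be either counted as event-free or removed. The document does not support that:

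- Statistical Analyses defines intention-to-treat as analysis by assigned arm, which a chi-square can respect.
- Drop-out is not defined as a lost outcome. A patient who stops study drug can still have a known 6-month status, and Randomization and interventions provides for visits at 1, 3 and 6 months and for telephone contact.
- A rule for unknown status may stand in the full protocol or analysis plan, which is not shown.

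Bias figures for losses counted as event-free would depend on that unstated rule and on an assumed split. With no true effect and a 10% event rate, the rejection rate is 5.0% for equal loss, 5.5% for 8% versus 12% and 8.4% for 5% versus 15%, if every event among the losses is missed. The document gives only 10% overall.

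Nor is it clear that a log-rank test should become primary. The stated endpoint is a rate at 6 months, and censoring at last contact has its own assumption of non-informative loss. Angiography recommended at 6 months may also bunch revascularizations around the cut-off.

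**Conclusion.** The point holds in a limited form. The stated primary test omits center and randomized statin, which makes it slightly conservative: type I error is about 4.8% to 4.9% at a 6% to 14% spread and about 3.9% at the extreme, against 4.8% to 5.0% for CMH. The power lost is 0 to about 1.7 points. These sizes rest on ten equal strata, complete outcomes and assumed stratum rates. Actual centers will differ in size, and the statin may have little effect on MACCE, in which case the gain is smaller still. The validity of the primary result is not in question.

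On follow-up, the finding is only that the planned time-to-event analysis is not aligned with the 6-month endpoint, in a plan that itself allows for 10% drop-out.

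**What to change.** 1. In Statistical Analyses, make the primary test a Cochran-Mantel-Haenszel test stratified by center and randomized statin. Report a stratified risk difference with 95% confidence interval, and keep the crude chi-square as supportive.
2. Add the Kaplan-Meier and log-rank analysis of time to first MACCE limited to 6 months, labelled as supportive of the primary endpoint. Use the same 6-month cut-off as the primary endpoint, so that events found at the 6-month angiography are handled alike in both. Keep the analysis over all follow-up for the 1- to 3-year question.
3. In Sample size calculation, say whether drop-out means a lost outcome or stopping study drug, so that the 864 and the 960 can be read together.

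Because the trial is open-label, the change should be dated before any comparison of outcomes by arm. If the full analysis plan already contains these items, only the article's wording needs aligning.

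The cost is a little more analysis work. Center, statin allocation and event dates are needed for the planned analyses anyway. Ten strata of about 96 patients each, if equal, are not sparse, and the required sample size is essentially unchanged.

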**Methods/Design:**

CILON-T trial was a prospective, randomized, open-label, multi-center, near-all-comer trial to demonstrate the superiority of triple anti-platelet therapy to dual anti-platelet therapy in reducing 6 months' major adverse cardiovascular/cerebrovascular events, composite of cardiac death, nonfatal myocardial infarction, target lesion revascularization and ischemic stroke. It also tested whether triple anti-platelet therapy is superior to dual anti-platelet therapy in inhibiting platelet reactivity in patients receiving percutaneous coronary intervention with drug-eluting stent. Total 960 patients were randomized to receive either dual anti-platelet therapy or triple anti-platelet therapy for 6 months and also, randomly stratified to either lipophilic statin (atorvastatin) or non-lipophilic statin (rosuvastatin) indefinitely. Secondary endpoints included all components of major adverse cardiovascular/cerebrovascular events, platelet reactivity as assessed by VerifyNow P2Y12 assay, effect of statin on major adverse cardiovascular/cerebrovascular events, bleeding complications, and albumin-to-creatinine ratio to test the nephroprotective effect of cilostazol. Major adverse cardiovascular/cerebrovascular events will also be checked at 1, 2, and 3 years to test the 'legacy' effect of triple anti-platelet therapy that was prescribed for only 6 months after percutaneous coronary intervention.

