## Methods/Design

### Study objectives, hypothesis and design

The primary objective of this study was to compare the efficacy of TAT with DAT in reducing 6 months' MACCE after PCI in those with documented CHD. The working hypothesis of this trial was 'TAT is superior to DAT in reducing 6 months' MACCE, the composite of cardiac death, nonfatal myocardial infarction (MI), ischemic stroke and target lesion revascularization (TLR) in CHD patients receiving PCI with DES'. The trial also addressed whether TAT is superior to DAT in reducing platelet reactivity and also, whether there is any clinical effect of statin-clopidogrel interaction on MACCE according to the type of statin. The protocol of the trial has been registered at http://www.clinicaltrials.gov (NCT00776828) and a brief flowchart of the whole study is summarized in Figure 1. The endpoints are summarized in Appendix 1.

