### Issues sought in the CILON-T trial

In addition to the primary endpoint of whether TAT would be superior to DAT in reducing the ischemic vascular events after PCI, CILON-T trial is planned to assess several issues that remains to be answered. The issue of whether laboratory benefits are directly connected with clinical outcomes will be sought. Specifically, there have been papers demonstrating that PRU levels predicted adverse cardiovascular events in high risk patients [31-33] and that cilostazol reduced the average level of platelet activation in patients with coronary heart disease [6] and also, PRU level [34]. However, racial difference is one factor that can influence the platelet reactivity [35] and there remains a paradox between the higher level of PRU and lower rate of thrombotic events after DES implantation in Asians. Simply compared, the rate of stent thrombosis involving more than 3,000 patients around 1.5 years after DES implantation is 1.9% in Europeans [36] while 0.77% in Japanese [2]. In this CILON-T trial, we can get valuable information whether cilostazol-induced reduction of PRU levels would lead to beneficial clinical outcomes.

It is also expected to shed light on whether non-CYP3A4-metabolized statin is superior to CYP3A4-metabolized statin in terms of MAC(C)E and if so, whether cilostazol would be effective in reducing this difference. In vitro studies have persistently suggested that the effect of clopidogrel would be reduced by concomitant use of lipophilic statin [37,38] but large in vivo studies do not show trend toward detrimental effect of these types of statin [16-18,39]. However, these in vivo results come from observational registry data or post-hoc analysis of randomized clinical trials. Therefore, our data would add additional information to clopidogrel-statin interaction issue and also, if any, a new finding on the effect of cilostazol in this drug interaction.

In conclusion, we still do not know whether TAT is superior to DAT in reducing MACCE after DES implantation for coronary heart disease in the unselected real-world patients. Furthermore, whether cilostazol-induced PRU level reduction will turn out to improve clinical outcomes has never been elucidated. We hope to address these issues in the CILON-T trial where we enrolled a large unselected population of patients treated with DES for significant coronary heart disease.

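### The randomized statin comparison is called both a priori and post-hoc, is worded by statin given, and as stated does not answer the question about cilostazol and statin

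*Protocol article*

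**What the plan says.** All places are in the protocol article.

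- **Allocation.** Under Randomization and interventions, patients are "randomly stratified to take equipotent doses of either atorvastatin 20 mg or rosuvastatin 10 mg per day before the interventional procedure". The abstract says the same: "randomly stratified to either lipophilic statin (atorvastatin) or non-lipophilic statin (rosuvastatin) indefinitely".
- **Aim.** Study objectives, hypothesis and design says the trial addressed "whether there is any clinical effect of statin-clopidogrel interaction on MACCE according to the type of statin". The Background and the Discussion section on issues sought add a further question: whether cilostazol can offset or reduce any such statin difference.
- **Endpoint status.** Outcome measures opens its list with "The key secondary endpoints defined a priori are" and includes "MACCE according to the type of statin and its interaction with clopidogrel". Appendix 1 repeats the item among the secondary endpoints.
- **Analysis.** Statistical Analyses states: "Also, most importantly, post-hoc analysis of MACCE according to the type of statin given (atorvastatin vs. rosuvastatin) will be done". The same section begins with "All analysis will be done by intention-to-treat method (all patients analyzed as part of their assigned treatment group" and confines per-protocol and as-treated analyses to description. It assigns a chi-square test to the clinical secondary endpoints.
- **View of earlier evidence.** Issues sought in the CILON-T trial notes of the large clinical studies that "these in vivo results come from observational registry data or post-hoc analysis of randomized clinical trials".

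**The concern.** The status of an analysis decides how its result may be read. A key secondary comparison of randomized groups, fixed in advance, is planned evidence. A post-hoc one is exploratory. The article gives the statin comparison both labels and, in the sentence that calls it post-hoc, also ranks it as most important. A reader of the results could not tell which applies, and could discount a valid randomized comparison for the very reason the article gives for discounting earlier studies.

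The word *given* raises a second doubt. Read literally it means the statin a patient took, not the one allocated. The statin is to continue indefinitely and MACCE is also checked at 1, 2 and 3 years, so the two groupings could come apart.

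Third, whether cilostazol reduces a statin difference is a question about two factors together. The comparison named involves only one of them.

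**Working it through.** **1. Status, place against place.** Three places treat the statin question as planned: the objectives, the list under Outcome measures and Appendix 1. One place, Statistical Analyses, calls it post-hoc. The endpoint (MACCE) and the factor (statin type) are the same in each, so these are not two different analyses.

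**2. Grouping.** The opening rule of Statistical Analyses covers all analyses and uses assigned groups. The statin sentence uses *given*. The general rule points to assignment, but the groups named in the primary endpoint and in the sample size are the two antiplatelet arms, and the rule does not say that it also covers the statin factor.

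**3. Question against method.** Every patient is to receive clopidogrel, so there is no arm without it. The randomized contrasts available are:

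- statin effect: atorvastatin rate minus rosuvastatin rate, over both antiplatelet arms;
- antiplatelet-by-statin interaction: (atorvastatin − rosuvastatin under dual therapy) − (atorvastatin − rosuvastatin under triple therapy).

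The stated comparison gives the first. Whether cilostazol reduces a statin difference is the second.

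**4. The plan's own figure.** Inputs from Sample size calculation: 10% against 5%, two-sided 5%, power 80%, 1:1, 10% dropout, t-test.

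n per arm = (1.960 + 0.842)² × (0.10 × 0.90 + 0.05 × 0.95) / 0.05² = 7.85 × 0.1375 / 0.0025 ≈ 432

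Total 864; 864 / 0.90 = 960. The stated 960 is reproduced. It is for the antiplatelet comparison only.

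**5. What that size offers the statin questions.** Assumptions not in the article: 1:1 statin allocation (hence 432 evaluable per statin, 216 per cell) and a mean rate of 7.5%, the midpoint of 10% and 5%.

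Statin effect, 432 per group:

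| True difference | Power |
|---|---|
| 2 points | 20% |
| 3 points | 39% |
| 4 points | 61% |
| 5 points | 80% |

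Interaction, with SE = √(Σ p(1−p)/n) over the four cells and power = Φ(d/SE − 1.96). The rate under triple therapy is 5% with either statin.

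| Rates by statin under dual therapy | d | Power, 216 per cell | Power, 240 per cell |
|---|---|---|---|
| 12% / 8% | 4 points | 20% | 22% |
| 12.5% / 7.5% | 5 points | 29% | 32% |
| 13% / 7% | 6 points | 39% | 43% |

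First row, 216 per cell: SE = √((0.1056 + 0.0736 + 0.0475 + 0.0475)/216) = 0.0356, and Φ(0.04/0.0356 − 1.96) ≈ 0.20. The 95% CI half-width is 1.96 × 0.0356 ≈ 7.0 percentage points.

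**The case against.** **The intention-to-treat rule already governs.** It covers all analyses, and as-treated results are descriptive only, so *given* is probably loose wording for assigned. This largely stands. A reader might infer that the plan throws away the second randomization. The article does not support that: the general rule points the other way, and a post-hoc label does not undo random allocation. What remains is an ambiguous word in the specific sentence, set against a general rule that does not mention the statin factor.

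**A bias figure would be speculative.** This also stands. Suppose 480 patients per statin, 7.5% in each (36 events), no true effect, 10% moving one way from atorvastatin to rosuvastatin, and movers at 15% (48 × 0.15 = 7.2 events). Rates by statin received are then 28.8/432 = 6.7% and 43.2/528 = 8.2%, a false gap of 1.5 points. With 5% moving it is 32.4/456 = 7.1% against 39.6/504 = 7.9%, about 0.8 points. If movers carry average risk it is 0. The article gives no switching rate, so the range of 0 to 1.5 points only illustrates why *assigned* should be written. It does not measure a defect.

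**An article may leave the interaction model to a fuller document.** A fair point, and the reason this part is the lesser one. But the article does name the comparison it regards as most important, and that comparison does not address a question the article itself raises. A reader might also infer that separate triple-against-dual tests within each statin are planned. They are not; the article names a comparison between the statins.

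**Only a secondary endpoint is touched.** Correct. The primary endpoint, its test and the 960 patients are unaffected.

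**Conclusion.** The point holds as an internal contradiction about a key secondary, randomized comparison. It is planned in three places and post-hoc in one, and its grouping is worded in a way that fits poorly with the section's own intention-to-treat rule. That conclusion rests on the text alone.

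The second part also holds, with less weight: the stated two-group comparison does not answer whether cilostazol reduces a statin difference. Under the assumptions shown (equal statin allocation, 216 to 240 per cell), interaction power is about 20% to 43%, so the estimate would be imprecise and a non-significant result would say little.

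This should be corrected before the statin results are analysed. It ranks below a defect that must be fixed for the trial to stand, because the primary analysis is untouched.

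**What to change.** In Statistical Analyses:

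1. Delete *post-hoc* and call MACCE by statin the pre-specified secondary comparison, in line with Outcome measures and Appendix 1. This assumes those sections reflect what was fixed in advance. If they do not, they are the ones to change.
2. Replace *statin given* with *statin assigned at randomization*, analysed by intention to treat. Keep statin received for description only.
3. Add the antiplatelet-by-statin interaction estimate with its 95% CI and the MACCE rates in the four cells, with a sentence saying the trial was not sized for the interaction.

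It would also help to describe the statin allocation under Randomization and interventions as a second randomization, since *randomly stratified* can be read as stratification.

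The cost is a few words and one additional model, using assignments already held in the randomization system. The sample size does not change.

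Suggested text: *MACCE by statin assigned at randomization is a pre-specified secondary comparison, analysed by intention to treat. The antiplatelet-by-statin interaction will be estimated with a 95% confidence interval and reported with the four cell rates; the trial was not sized for this interaction. Results by statin received are descriptive.*

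### Repeated-measures ANOVA for platelet reactivity discards patients without a 6-month sample and leaves the TAT-versus-DAT test unnamed; a mixed model with named contrasts is a cost-free improvement

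*Protocol article*

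**What the plan says.** The protocol article, under *Study objectives, hypothesis and design*, sets a question about levels between arms: "The trial also addressed whether TAT is superior to DAT in reducing platelet reactivity". *Outcome measures* lists PRU first among the key secondary endpoints and names no time point.

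*Randomization and interventions* gives two sampling times. The first is "immediately before discharge". The second follows: "Platelet reactivity was also measured at 6 months after index procedure". Both fall after the start of study treatment, since "A loading dose of cilostazol (Otsuka Korea) 200 mg was given immediately before the procedure", and the abstract gives the assigned treatment a duration of 6 months. The same section lets sites follow patients "either by office visits or by telephone contacts as necessary".

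*Statistical Analyses* gives the method in one sentence: "Analysis of platelet function will be tested using repeated ANOVA method with the Bonferroni's correction". It names no deciding term or time point, and does not say what the Bonferroni correction covers. The same section opens with: "All analysis will be done by intention-to-treat method (all patients analyzed as part of their assigned treatment group".

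**The concern.** There are two difficulties.

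First, classical repeated-measures ANOVA needs a complete pair from each patient. A randomised patient with a discharge PRU but no 6-month PRU leaves the analysis altogether, so an observed value is thrown away. Some loss is foreseeable: the sample size allows for 10% drop-out, and a telephone contact yields no blood sample. In an open-label trial the 6-month sample also depends on survival, tolerance and attendance. If these differ between arms and relate to PRU, the complete-pair comparison is no longer protected by randomisation.

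Second, a two-arm, two-visit ANOVA gives three tests: arm, visit and arm-by-visit. They answer different questions, and the article does not say which one decides whether TAT lowers PRU. With both samples on treatment, arm-by-visit asks only whether the gap between arms changes between discharge and 6 months.

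At stake is the laboratory conclusion that the discussion intends to link to clinical outcome.

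**Working it through.** **The plan's own figure.** *Sample size calculation* assumes MACCE of 10% and 5%, two-sided 5% significance, 80% power, 1:1 allocation and 10% drop-out. With unpooled variance:

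- n per arm = (0.10 × 0.90 + 0.05 × 0.95) × (1.960 + 0.842)² / 0.05² = 0.1375 × 7.85 / 0.0025, which rounds up to 432.
- 432 / 0.90 = 480 per arm, or 960 in total.

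The 960 reproduces, but it concerns MACCE. The article gives no size, SD or effect for PRU.

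**Patients left with complete pairs.** Applying the 10% to the 6-month sample is an assumption, as are the higher rates, and all 960 are taken to have a discharge sample.

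| 6-month sample missing | Complete pairs of 960 | Removed |
|---|---|---|
| 10% | 864 | 96 |
| 20% | 768 | 192 |
| 30% | 672 | 288 |
| 40% | 576 | 384 |

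At 10%, the standard error of the discharge contrast grows by √(960/864) = 1.054.

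**What each term tests.** Let d₀ and d₆ be the TAT-DAT differences at discharge and at 6 months. The arm main effect tests (d₀ + d₆)/2, which is a t-test on each patient's mean. Arm-by-visit tests d₆ − d₀, which is a t-test on each patient's change. If d₀ = d₆, the second quantity is zero whatever the size of the effect, so the test rejects at its nominal level.

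**Simulation.** All PRU values are assumed: mean 230, SD 80, correlation 0.5 between visits, 480 per arm, 2,000 runs per scenario. Loss is at random and equal in both arms.

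| TAT reduction at discharge / 6 months | Missing | Arm main effect rejects | Arm-by-visit rejects |
|---|---|---|---|
| 20 / 20 | 10% | 99.2% | 5.2% |
| 20 / 20 | 30% | 95.8% | 4.8% |
| 20 / 20 | 40% | 92.8% | 6.0% |
| 40 / 20 | 10% | 100% | 95.8% |

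A hand check of the first row: the SD of a patient's mean is 80 × √((1 + 0.5)/2) = 69.3. The standard error is 69.3 × √(2/432) = 4.71. Then 20/4.71 = 4.24, and power is Φ(4.24 − 1.96) = 98.9%, in line with the simulation. In the last row arm-by-visit rejects because the effect wanes.

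**Bias if loss depends on outcome.** This is an illustration only: no true effect, 20% of DAT lost at random, and about 30% of TAT lost, more often when 6-month PRU is high. The complete-pair main effect is then off by about 12 PRU and rejects in 65% of runs. A comparison of all discharge samples rejects in about 6%.

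**The case against.** The strongest reply is that the article states no exclusion rule and selects no term, and that both could properly sit in a fuller protocol or SAP that is not shown. Much of this stands, and it rules out several stronger readings.

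- *That the plan tests TAT by arm-by-visit and so cannot detect a steady reduction.* A reader might infer this, but the article never names that term. The same ANOVA has an arm main effect that does test average PRU. Bonferroni could even refer to contrasts at each visit.
- *That the plan contradicts its own intention-to-treat rule.* The parenthesis fixes the arm in which a patient is counted, in contrast with the per-protocol and as-treated analyses. It does not say how missing samples are handled. Complete pairs are the default of the named method, not a stated rule, so this is tension and not contradiction.
- *That at least 96 patients would be lost.* The 10% is a planning allowance for MACCE and no lower bound. All patients were recommended angiography at 6 months, so attendance at that time was expected.
- *That the absence of a pre-drug sample is an error.* Randomisation makes on-treatment levels comparable between arms.
- *That leaving out statin biases the result.* Statin was itself randomised, so its omission does not bias the arm contrast, and the article lists no model terms at all.

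The article's general rule for continuous variables, an unpaired t-test or Mann-Whitney test, might also allow discharge PRU to be compared in everyone sampled. But platelet function has its own sentence, and that sentence names repeated ANOVA. The named method is a commitment in the text, and its ordinary form discards observed data. That part of the point survives.

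**Conclusion.** The point holds as an improvement to a key secondary analysis; the analysis is not wrong as written. The named method can answer the PRU question through its arm main effect. Its drawbacks are that, in classical form, it drops patients who lack one of the two samples, and that the deciding test is left open.

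The loss of precision is small: about 5% on the standard error of the discharge contrast if 10% of 6-month samples are missing. The larger risk is bias from loss related to tolerance or outcome. The documents give no figure for that, and the 12 PRU above rests wholly on an assumed pattern of loss. The choice of term matters more: under a constant assumed reduction of 20 PRU, one term rejects in about 99% of runs and another in about 5%. The primary MACCE analysis is not touched.

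**What to change.** Replace the repeated ANOVA with a linear mixed model for repeated measures on all available PRU values, by assigned arm. Include arm, visit and arm-by-visit, the randomised statin and the stratification factor center, with an unstructured covariance between the two visits. Name the TAT-DAT contrasts at discharge and at 6 months as the tests of the platelet hypothesis, and state that Bonferroni covers these two, each at 0.05/2 = 0.025.

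Every patient with at least one sample then contributes, and the discharge contrast uses all discharge samples. The model relies on loss being explained by the observed data. If loss depends on the unseen 6-month value itself, the 6-month contrast can still be biased, so the number of samples by arm and visit should be reported beside it.

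The cost is a few lines of analysis text and standard software. No new data are needed.
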